## Abstract

**Background:**

Laparoscopic surgery has become the preferred approach for many procedures because of reduced post-operative pain, better recovery, shorter hospital stay and improved cosmesis. Single incision laparoscopic surgery is one of the many recent variants where either standard ports or a specially designed single multi-channel port is introduced through a single skin incision. While the cosmetic advantage of this is obvious, the evidence base for claims of reduced morbidity and better post-operative recovery is weak. This study aims to compare the effectiveness of single port/incision laparoscopic appendicectomy with standard three-port laparoscopic appendicectomy in adult patients at six weeks post-surgery. We also wish to assess the feasibility of a multicentre randomised controlled trial comparing single port/incision laparoscopic surgery with standard three-port laparoscopic surgery for other surgical techniques.

**Methods and design:**

Patients diagnosed with suspected appendicitis and requiring surgical treatment will be randomised to receive either standard three-port or single incision laparoscopic surgery. Data will be collected from clinical notes, operation notes and patient reported questionnaires. The following outcomes will be considered:

1. Effectiveness of the surgical procedure in terms of:

•patient reported outcomes

•clinical outcomes

•resource use

2. Feasibility of conducting a randomised controlled trial (RCT) in the emergency surgical setting by quantifying:

•patient eligibility

•randomisation acceptability

•feasibility of blinding participants to the intervention received

•completion rates of case report forms and patient reported questionnaires

**Trial registration:**

ISRCTN66443895 (assigned 10 March 2011, first patient randomised 09 January 2011)

## Background

Appendicectomy is one of the most commonly performed surgical procedures in general surgery. In England (2010 to 2011), appendicectomy resulted in 47,145 operations; 41,458 of which were for an emergency admission [1]. Laparoscopic surgery is the preferred approach for many abdominal procedures because of reduced postoperative pain, more rapid recovery and improved cosmesis, which follow a successful operation compared with a conventional single large incision. Whilst the long term clinical result may be similar [2], the perception amongst many patients and surgeons of advantage in terms of these short-term outcomes is a powerful influence on practice. There are continuing developments to laparoscopic surgery to reduce the size, number and placement of incisions to both improve the cosmetic appearance and reduce abdominal wall trauma.

One of the recent innovations is Single Incision Laparoscopic Surgery. This can be either insertion of multiple ports through a small incision or through a proprietary device with multiple channels. The fundamental difference to conventional multi-port laparoscopic surgery is to place all the ports through a single incision which, when sited in the umbilicus, can result in no visible scar in the abdominal wall.

The current literature largely comprises case reports and small series detailing single port methods [3-9]. The technique has been used to perform a large variety of procedures including appendicectomy, cholecystectomy, nephrectomy, hysterectomy, oophorectomy, adrenalectomy, gastric bypass, Nissen fundoplication, hernia repair, splenectomy, colon resection and liver resection. Apart from a handful of reported randomised controlled trials (RCTs) [3-9] the evidence base is weak and insufficient to inform practice and robustly assess claims of reduced pain and morbidity with improved cosmesis and faster recovery are unsubstantiated [10-15]. In general, it is perceived that the single port/incision technique takes longer initially than conventional laparoscopic surgery and the differences in costs and safety are unknown.

Nevertheless, there is considerable interest in introducing single port/incision surgery and there are a large number of training courses. The public perception is that it might become the procedure of choice if it becomes available [16]. It is crucial that the technique be critically evaluated during the introductory phase of implementation to provide objective data to inform further adoption and evaluation. However, the difficulty of undertaking such an evaluation has been succinctly stated in Buxton’s law: “It is always too early [for rigorous evaluation] until, unfortunately, it’s suddenly too late” [17]. The introduction of laparoscopic surgery for Cholystectomy is a vivid example of the *ad hoc* nature in which a new surgical intervention can be introduced into practice and the difficulties of conducting rigorous evaluations of its value [18]. Ideally, a definitive evaluation requires a large, multicentre RCT of single port versus three-port surgery. Currently, there is a paucity of data to help plan and design such a large RCT. Additionally, further refinement of the single port/incision methodology is needed. There is, therefore, an urgent need for a well conducted feasibility study to provide preliminary results and inform the planning of such a large RCT (for example, how to define the intervention, which outcomes to use and when; likely throughput rates; estimates of conversion rates). It is hoped that the results of this study will lead to a large multicentre RCT of single versus standard three-port laparoscopic surgery.

This study will compare the effectiveness of single port/incision laparoscopic appendicectomy with standard three-port laparoscopic appendicectomy in adult patients at six weeks post-surgery. Additionally, it will inform the feasibility of more complex single port techniques, such as cholecystectomy. Appendicectomy is the focus of this study because it is a common and relatively simple procedure to undertake. Currently, no RCTs of single port versus three-port surgery have been published [8].

The specific objectives are:

•To compare the interventions in terms of patient reported outcomes, clinical measures and resource use.

•To assess the feasibility of a randomised controlled trial evaluating another single port/incision operation by quantifying patient eligibility and acceptability, feasibility of blinding participants to the intervention received and surgeon perception of interventions.

## Methods and design

Figure 1 provides an overview of the trial’s methodology.

**Figure 1 F1:**
[figure not shown]
Trial flow diagram.

### Inclusion and exclusion criteria

#### Inclusion criteria

Patients aged 16 years and over presenting with suspected appendicitis for whom laparoscopic surgical management is judged appropriate are eligible for inclusion.

#### Exclusion criteria

1. Patients who have had previous open abdominal surgery through midline incision.

2. Patients who have had previous umbilical hernia repair with mesh.

3. Patients unable to consent.

### Trial interventions

Participants will receive the allocated intervention, either single port/incision laparoscopic surgery (SPILS) or standard three-port laparoscopic appendicectomy surgery. The surgical interventions will be delivered or supervised by a surgeon who has expertise in the specific intervention. All participating surgeons will have completed appropriate surgical training. Further details of the interventions are given below:

#### SPILS

A single intra-umbilical incision will be made and a multi-channel port will be inserted. A 5 mm, 30 degree telescope will be used to visualise the operative field. Conventional laparoscopic instruments will be used for the procedure. Roticulating/curved instruments will be available and used if required. Use of any additional instruments or ports will be recorded. The musculo-aponeurotic layers of the port site will be closed with absorbable sutures before closing the skin incision.

#### Standard three-port laparoscopic surgery

Pneumoperitoneum will be established by an open technique through an intra/supraumbilical incision with a 10 to 12 mm port for initial pneumoperitoneum and inspection. A further 5 or 10 mm port will be used in the left iliac fossa (depending on the availability of 5 mm laparoscopes) and a 5 mm port will be used in the hypogastrium. Standard laparoscopic instruments will be used for the procedure as per existing hospital protocol. The musculo-aponeurotic layers of port sites of 10 mm and over will be closed with absorbable sutures before closing the skin.

The routine surgical technique will be dissection of the mesoappendix from the appendix with diathermy and division of the appendix base between two endoloops. In more complicated cases, alternative techniques may be used. Any variations to the regimen with justification will be recorded.

A standard pain relief policy will be followed, where possible. This will include one or more of the following postoperative analgesics: paracetamol (1g QID); dihydrocodeine, diclofenac and morphine (doses will be titrated and recorded).

### Identification and enrolment of potential participants

Patients likely to require surgery for acute appendicitis and who meet the eligibility criteria will be identified in the general surgery units by the consultant or designated team member. The consultant or team member will introduce the study to the patients and provide further details of the study by means of the Patient Information Sheet.

The participants will keep a copy of the Patient Information Sheet and the consent form (one copy will be filed in the hospital notes, one given to the participants and the top copy returned to the SCARLESS co-ordinating office in Aberdeen). A letter and General Practitioner (GP) Information Sheet will be sent to the participant’s GP. Participants who initially agree to enter the study but later decide to withdraw or become unable to continue will be asked for consent to enable us to access relevant NHS data in the future.

Patients who are ineligible or who do not agree to participate in the study will be logged anonymously along with a minimum dataset including gender, year of birth and reason(s) for declining (if offered).

### Randomisation and allocation

Participants will be recruited from a single centre, Aberdeen Royal Infirmary (UK). Following consent and collection of baseline data, the local consultant/designated team member will randomise the patient.

Participants will be randomised to one of the two study groups in equal proportion using the randomisation application at the trial office at the Centre for Healthcare and Randomised Trials (CHaRT), Aberdeen. Randomisation will be stratified by gender and computer generated permuted blocks of varying size used within each stratum. This randomisation application will be available 24 hours a day, seven days a week as an Interactive Voice Response (IVR) telephone system. Due to the acute nature of the admission to surgery and potential difficulty in tracking patients, date of birth will also be recorded in the randomisation process and available, if necessary, for use in addition to the study number to identify patients. The date of birth will not be openly available.

### Concealment of group allocation to participants

The feasibility of concealing group allocation from the participants and the ward staff will be investigated. Although blinding in the theatre is not possible given this is a surgical trial, participants will not be informed after their surgery of the procedure actually carried out. Blinding of participants will be attempted by using three hypoallergenic dressings applied at the umbilicus, in the left lower quadrant and hypogastrium unless conversion to open abdomen is required.

### Sample size

As there were no published RCTs comparing single port laparoscopic appendicectomy with standard three-port laparoscopic appendicectomy when the study was designed [8], a formal sample size calculation based upon previous data was not possible. A sample of 80 participants recruited is anticipated over the seven-month recruitment phase. Adopting a 5% two-sided significance level, this would allow an effect size (Cohen’s d) of 0.65 to be detected with 80% power for patient reported measures, such as the Body Image Questionnaire [19]. Binary feasibility measures are likely to be estimated with a (one-group) confidence interval of between 10 and 20% depending upon the corresponding event rate [19].

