#### Feasibility measures

Feasibility measures include eligible patients per month; proportion formally considered for trial entry; proportion randomised (and reasons why not); proportion who are unaware of their received intervention at 24 hours; proportion of those recruited with complete data set at six weeks; surgeon’s perception of SPILS approach and the suitability of available equipment.

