### Statistical analyses

For feasibility measures, such as the proportion of eligible patients who consent to randomisation, the frequency and corresponding 95% confidence interval will be calculated. Patient-reported and clinical measures will be summarised using appropriate summary measures (for example, frequency or mean and standard deviation) for each treatment group. The treatment groups will be compared at the two-sided 5% significance level. BIQ and pain NRS (area under the curve over a seven-day period) will be analysed using an independent *t*-test. Other outcomes will be assessed using standard statistical methods as appropriate, for example, comparison of proportions Newcombe’s CI method [21] or chi-squared test for trend [22], and independent *t*-test for binary and continuous outcomes respectively. Corresponding 95% confidence intervals will also be calculated. A single principal analysis is anticipated at the end of the study following intention to treat principle (grouped according to allocation). No imputation for missing data will be carried out. All analyses will be conducted using Stata 12 [23].

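### The 80% power at d = 0.65 is stated for 80 recruited participants with no allowance for unreturned six-week questionnaires; the accompanying confidence interval range is also unclear

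*Protocol article*

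**What the plan says.** The Sample size section explains that no earlier trial data were available for a formal calculation and works from expected recruitment: "A sample of 80 participants recruited is anticipated over the seven-month recruitment phase". It continues: "Adopting a 5% two-sided significance level", this sample would allow an effect size (Cohen's d) "of 0.65 to be detected with 80% power for patient reported measures, such as the Body Image Questionnaire". On precision it adds: "Binary feasibility measures are likely to be estimated with a (one-group) confidence interval of between 10 and 20" per cent, depending on the event rate.

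Four other places bear on the power figure:

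- **Outcome measures and Table 1.** The BIQ is a primary effectiveness outcome. It is collected once, by postal questionnaire at six weeks, and Table 1 shows no baseline BIQ.
- **Monitoring the participants.** Non-return of questionnaires is expected to occur and is met with a postal reminder or a telephone call.
- **Feasibility measures.** One quantity that the trial sets out to estimate is the "proportion of those recruited with complete data set at six weeks".
- **Statistical analyses.** "BIQ and pain NRS (area under the curve over a seven-day period) will be analysed using an independent" t-test, and "No imputation for missing data will be carried out".

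**The concern.** Power depends on the number analysed, but the protocol attaches its power figure to the number recruited. For the BIQ the two will differ unless nearly every participant returns the six-week questionnaire. With no baseline measurement and no imputation, a participant who does not return it adds nothing to the BIQ comparison. The protocol itself treats completeness as unknown.

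At stake is how the BIQ result is read. A reader who relies on the stated 80% would take a non-significant difference as stronger evidence against d = 0.65 than the data are likely to give. The Background says the study is meant to inform planning of a larger trial, so a realistic statement of what 80 recruits can show is useful in itself.

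The precision sentence has a lesser fault. Without knowing whether 10 to 20% is a full width or a half-width, and on how many people, a reader cannot check it or use it.

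**Working it through.** **Inputs from the protocol article.** 80 recruited; two-sided 5% level; d = 0.65; 80% power (all Sample size). Allocation is equal, "Participants will be randomised to one of the two study groups in equal proportion" (Randomisation and allocation), so 40 per arm. The test is an independent t-test, and feasibility intervals are at 95% (Statistical analyses).

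**Input assumed.** The document gives no return rate. I use 90% and 80%, with losses spread equally over the arms.

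**Step 1: reproduce the stated power.** With n analysed per arm, the t-test has 2n − 2 degrees of freedom and noncentrality d × √(n/2). At n = 40 the noncentrality is 0.65 × √20 = 2.907 and the power is 81.9%. The normal approximation gives Φ(2.907 − 1.960) = Φ(0.947) = 82.8%. The stated 80% is therefore correct for 80 analysed.

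**Step 2: find the margin.** By the normal approximation, n per arm = 2 × (1.960 + 0.842)² / 0.65² = 37.2, so 38 per arm or 76 in total. The t-test needs 38.14, so 39 per arm or 78 in total. The margin is 80 − 78 = 2 to 80 − 76 = 4 participants, a loss of 2.5% to 5%.

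**Step 3: allow for non-return (t-test).**

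| Analysed | Return | Power at d = 0.65 | d detectable with 80% power |
|---|---|---|---|
| 80 | 100% | 81.9% | 0.634 |
| 78 | 97.5% | 80.9% | 0.643 |
| 76 | 95% | 79.9% | 0.651 |
| 72 | 90% | 77.6% | 0.670 |
| 64 | 80% | 72.6% | 0.711 |

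The normal approximation gives 78.8% at 72 and 73.9% at 64, so the choice of method moves the result by little more than one point. The type II error at d = 0.65 goes from the stated 20% to 100 − 77.6 = 22.4% or 100 − 72.6 = 27.4%.

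**Step 4: confidence interval range.** Read as the full width of a 95% Wald interval on 80 people, the width is 2 × 1.96 × √(p(1 − p)/80):

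| Rate p | Full width, n = 80 (percentage points) |
|---|---|
| 5% | 9.6 |
| 10% | 13.1 |
| 20% | 17.5 |
| 30% | 20.1 |
| 50% | 21.9 |

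The table is symmetric about 50%. The width passes 20 points at p = 29.6% and falls back below it at 70.4%. The largest excess is 21.9 − 20 = 1.9 points. At 50% the Wilson interval is 21.4 points wide and the exact interval 22.8, so the small excess does not come from the choice of method.

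**The case against.** **The calculation is not wrong.** This stands: Step 1 reproduces it. The fault is only that a figure valid for 80 analysed is stated for 80 recruited.

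**The reduced power rests on an assumption, and reminders are planned.** This also stands. A return of about 97.5% would preserve the stated figure. But the protocol gives no ground for expecting so high a return, and it makes completeness something to be found out.

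**The article may have left an attrition allowance to a fuller document.** If the finding were only that an allowance is absent, this would answer it. The article, however, makes an explicit power claim and ties it to the number recruited, and that claim depends on near-complete return.

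**The sample was set by recruitment, and 0.65 is descriptive.** True, and it limits the importance of the point. No design decision hangs on 0.65 against 0.67 or 0.71. The 95% intervals planned for the treatment comparisons will also show the precision actually reached.

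**The confidence interval sentence is hedged.** It speaks of what is likely and of dependence on the event rate. A reader might infer that the range is simply wrong, but the text does not support that. On the full-width reading at n = 80, rates of about 5.5% to 29.6% and 70.4% to 94.5% fall inside it. If 'one-group' means one arm of 40 and the figure is a half-width, rates of 10% to 50% give 9.3 to 15.5 points, roughly within the range. Some proportions, such as eligible patients randomised, have a denominator of 80 or more and so can have narrower intervals.

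A reader might also apply the range to the surgeon's perception of the single-port approach and the suitability of equipment, with about 40 observations and widths of up to 31 points. The sentence covers binary measures. Nothing in the article says that these two items are binary or that the range was meant for them.

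**Conclusion.** The power statement should be corrected as a matter of wording. It is right only if about 76 to 78 of the 80 recruits are analysed for the BIQ. With assumed returns of 90% or 80%, power at d = 0.65 is about 78% or 73%, and the detectable d with 80% power is about 0.67 or 0.71. These figures assume equal loss in the two arms and the planned t-test. The return rates are mine.

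It would go too far to conclude that the sample size was miscalculated or that 80 is too few for a feasibility study: the figure reproduces, and the document presents 80 as what recruitment is expected to yield.

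The confidence interval point is minor. The range is ambiguous about width and denominator. On the full-width reading at n = 80 it is about 2 points too narrow for rates near 50%, and it is exceeded only between about 30% and 70%.

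**What to change.** Keep 80 and restate the two sentences, for example:

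> Assuming that 80–90% of the 80 participants return the six-week questionnaire, d of 0.67 to 0.71 is detectable with 80% power. For binary feasibility measures on all 80 participants, the full 95% CI width will be about 10 to 22 percentage points for rates of 5% to 50%.

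If the investigators expect a different return rate, they should state it and take the matching detectable effect from the same calculation.

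The cost is two reworded sentences and slightly less favourable stated figures, with no extra patients and no change to the analysis. Keeping 0.65 instead would mean recruiting 78/0.9 = 86.7, so 87, at 90% return, or 78/0.8 = 97.5, so 98, at 80% return. Both exceed the 80 expected in the seven-month recruitment phase.

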### Subsequent tasks

Following formal trial entry -

The Study Office will:

i. Inform the participant’s GP (by letter enclosing information about SCARLESS and Study Office contact details).

ii. Process the pain Numerical Rating Scale (NRS) seven-day diary and the six-week participant questionnaire.

iii. Collect the feasibility measures.

The consultant or team member will:

i. Provide the original signed consent form to the Study Office and file the Hospital Copy of the form in the hospital notes along with information about SCARLESS.

ii. Inform the ward and theatre staff as appropriate of the participant’s study participation and intervention allocation.

iii. Complete case report forms (CRFs) as appropriate and either enter the data directly onto the SCARLESS website or forward the hard copies of the CRFs to the co-ordinating office at CHaRT for electronic data entry. The data to be collected include data required to complete randomisation; intra- and postoperative.

iv. Return all study documentation to the Study Office (CHaRT, Aberdeen) for archive.

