### Reporting responsibilities of the CI

The Chief Investigator (CI) or deputy will be automatically notified of all SAEs. If, in the opinion of the local surgeon and the CI, the event is confirmed as being related and unexpected, the CI will submit a report to the main REC and the study sponsors within 15 days of the CI becoming aware of it.

As the trial arm to which participants are allocated cannot be blind to the operating surgeons or theatre staff after randomisation has occurred, unblinding is not an issue in this trial. A record of the operative procedures actually carried out will be available in the medical notes if required clinically.

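### The protocol sets out to investigate concealing allocation from ward staff, but one of its task lists has the team tell ward staff the allocation

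*Protocol article*

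**What the plan says.** Three parts of the protocol article bear on who may know the allocation.

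- **Concealment of group allocation to participants.** The aim covers two groups: "The feasibility of concealing group allocation from the participants and the ward staff will be investigated". One exemption is made: "Although blinding in the theatre is not possible given this is a surgical trial". For participants there are two concrete measures. They are not told after surgery which procedure they had, and dressings hide the difference: "Blinding of participants will be attempted by using three hypoallergenic dressings applied at the umbilicus, in the left lower quadrant and hypogastrium", except after conversion to open surgery.
- **Subsequent tasks.** Under the lead-in "Following formal trial entry", item ii for the consultant or team member reads: "Inform the ward and theatre staff as appropriate of the participant’s study participation and intervention allocation".
- **Reporting responsibilities of the CI.** Having noted that operating surgeons and theatre staff cannot be blind, the article states that "unblinding is not an issue in this trial". It adds that the record of the procedure performed is in the medical notes for clinical need.

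The objective at the end of the Background is "feasibility of blinding participants to the intervention received and surgeon perception of interventions". The matching item under Feasibility measures is "proportion who are unaware of their received intervention at 24 hours".

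**The concern.** Staff who have been told the allocation cannot also be the group in whom its concealment is tried out. Item ii puts ward and theatre staff in one instruction and names the allocation among the things to be passed on, although the concealment section treats the two groups differently.

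Two further things are at stake.

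- **The blinding result.** The trial is meant to inform a larger one, and the feasibility of blinding participants is among its stated objectives. If the ward has been told, a low proportion unaware at 24 hours could mean that the dressings failed, or that staff who had been informed let the allocation slip. The measure alone would not separate the two.
- **Early pain and analgesia.** Pain on days one to seven is a primary effectiveness outcome that participants rate themselves, and it is analysed as an area under the curve. Analgesic use is also an outcome, and some doses are titrated. Both could be influenced by carers or participants who know the allocation.

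**Working it through.** There is no figure to recompute. The check sets the sections side by side, group by group.

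| Group | Concealment section | Subsequent tasks, item ii | Listed measure of blinding |
|---|---|---|---|
| Theatre staff | Exempt | Told participation and allocation, as appropriate | None needed |
| Ward staff | Concealment to be investigated | Told participation and allocation, as appropriate | None listed |
| Participants | Concealment to be investigated; not told, three dressings | Not addressed | Unaware at 24 hours |

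1. **Theatre staff.** The two sections agree.
2. **Ward staff.** They conflict. The concealment section does not exempt the ward, and item ii does not separate it from the theatre. No other section gives the ward its own rule or restricts what it hears to study participation.
3. **Participants.** There is no direct conflict, because item ii does not have anyone tell the participant. The link is indirect: an informed ward is one more route by which the participant may find out.
4. **Timing.** The lead-in to the task list sets only the earliest point, trial entry. Randomisation follows consent and baseline data, so the ward could be told well before the 24-hour check. Nothing defers the disclosure until after it.
5. **Route to the outcomes.** Pain is recorded by the participant in a diary, so any effect has to pass through disclosure to the participant or through altered care. The analgesic policy, given under Standard three-port laparoscopic surgery, says that doses are titrated and recorded but not by whom. That ward staff have a part in it is an inference. Length of stay is not given, so the share of the seven days spent under ward care is unknown.
6. **The serious adverse event section.** It names only surgeons and theatre staff as unable to be blind, which matches the exemption in the concealment section. It does not add a second contradiction.

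**The case against.** The strongest reply has four parts.

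- **No promise of concealment was made.** The article undertakes only to investigate its feasibility, under a heading that mentions participants alone. This is correct, and the point should not be put as a broken commitment. It does not remove the conflict, because feasibility cannot be investigated in staff who have been given the answer.
- **The qualifier *as appropriate* resolves it.** With two audiences and two pieces of information, the sentence could mean that the ward hears of participation and the theatre hears the allocation. That reading is open, but the text does not state it, and team members could apply the line differently. So the article does not establish that ward concealment is bound to fail.
- **The listed objective and measure concern participants.** This stands. A reader might infer that the blinding-feasibility result becomes uninterpretable. The article does not support that: the dressings and the rule against informing participants remain, and the 24-hour proportion would still show how many stayed unaware under the procedures actually used. What is lost is clarity about why any of them became aware.
- **Bias is asserted, not shown.** This also stands. A reader might infer that the pain and analgesic comparisons are biased. The article supports only a plausible route, with no direction or size.

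It is also tempting to read the statement that unblinding is not an issue as dismissing blinding altogether. In its place among the reporting duties, it more naturally means that no code-break procedure is needed for a serious adverse event. It is loose wording at most.

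**Conclusion.** The concealment section and item ii of the task list do not fit together for ward staff and need to be reconciled. Where the ward is told the allocation, the ward-staff part of the concealment question cannot be answered. For participants, and for early pain and analgesic use, the consequence is an avoidable risk.

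The reach is at most the 80 planned participants. How many are actually affected depends on how the team reads the qualifier, which the article does not say. The size of any effect on the outcomes cannot be derived from the article. No listed objective, endpoint or analysis is invalidated by this point, and the six-week body image outcome is not part of it.

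The conclusion assumes that item ii is carried out as worded for at least some participants. The risk to pain and analgesic use also assumes that ward staff have a part in postoperative care within the first seven days.

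**What to change.** Reword item ii so that theatre staff are told of study participation and allocation, while ward staff are told of study participation only. State that the operative record in the medical notes remains available to the ward if clinically required, which the article already provides for.

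Optionally, add a few words under Reporting responsibilities of the CI to make clear that the remark about unblinding refers to surgeons and theatre staff. A log of unblinding events would be a refinement; this point does not depend on one.

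The article's registration entry records that a first patient has already been randomised. For participants already treated, the rewording comes too late, so the report should say what ward staff were in practice told.

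The cost is a change of wording and a briefing for staff, with no extra participants or procedures. The small downside is that ward staff must go to the notes when they need the operative detail, and those who do so will then know the procedure.
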